##### Standard errors

We will estimate Huber–White robust standard errors in all analyses.

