## Methods/design

### Study design

This study will use a three-armed randomized controlled trial (two intervention groups and one control group), with randomization at the individual level. The intervention will last for 24 months. See the SPIRIT checklist for a guide to the key items reported in this protocol (Additional file 1).

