##### Percentage of prescribed medication taken

Our behavioral primary outcome will be electronically monitored adherence. MEMS data will be collected continuously during the 24 months of the intervention period as well as for 12 months after the intervention ends, allowing us to investigate daily adherence and its timing. We will create a variable that captures the proportion of prescribed pills that were actually taken (i.e. number of actual bottle openings divided by the prescribed bottle openings).

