### Sample size and power

We have calculated the size of effects that our sample will be able to detect with 80% power (two-tailed test) with regard to outcomes at months 12 and 24, and 10% attrition every year (we observed 5% attrition over 20 months in our previous studies so this is a conservative estimate). For the primary outcome of viral suppression, we use a conservative estimate of 70% of clients in the control group showing suppression, based on discussions with the Mildmay team. Our sample size of 110 participants in each of the three arms (total *n* = 330) will be able to detect a 7 percentage point difference for joint comparison of T1 and T2 against the control group at month 12, and about an 8.5 percentage point difference between the two intervention arms (a subgroup analysis). The corresponding differences at month 24 are 8 and 9 percentage points, respectively. These are considered small effect sizes (Cohen’s *d* of between .15 and .185), which we will be able to detect. For adherence, in our previous study we observed mean adherence rates of ~75% as measured by MEMS caps. Our sample size of 110 in each of the intervention arms and the control group will provide sufficient power to detect about a 6.5 percentage point difference in mean adherence between the two intervention arms (combined) and the control group. To test for differences in adherence between the two intervention arms, our study is powered to detect about a 7.5 percentage point effect as measured by MEMS caps. Again, this means we will be able to detect small effects. The corresponding differences we will be able to detect at month 24 are about 7 and 8 percentage points, respectively. Our main econometric models will include covariates that will improve precision. Therefore, these minimum detectable effects reported above are likely upper bounds.

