##### Estimating impact on adherence

To estimate the impact of our interventions on treatment adherence, we will use an ordinary least squares regression of the following forms:

Unadjusted:
3$$ {y}_{it}={\beta}_0+{\beta}_1T{1}_{it}+{\beta}_2T{2}_{it}+{\lambda}_t+{\epsilon}_i $$

Adjusted:
4$$ {y}_{it}={\beta}_0+{\beta}_1T{1}_{it}+{\beta}_2T{2}_{it}+{\lambda}_t+{\boldsymbol{X}}_{\boldsymbol{i}}\boldsymbol{\alpha} +{\epsilon}_i $$

where *y*_*it*_ represents the proportion of the prescribed bottle openings that were opened by individual *i* at time *t*. In this model, *β*_1_ represents the impact of T1 on the proportion of pills taken in a given month and *β*_2_ represents the impact of T2 on the proportion of pills taken in a given month. *λ*_*t*_ represents an indicator for each time period. Equation 4 includes the term ***X***_***i***_, which represents the same covariates as in Eq. 2.

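### The pooled adherence models (Eqs. 3–4) stack repeated months per participant, but the only stated variance rule, Huber–White, does not by itself allow for within-person correlation

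*Protocol article*

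**What the plan says.** All references are to the protocol article.

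- **Model.** For adherence, under Estimating impact on adherence, "we will use an ordinary least squares regression of the following forms" (Eqs. 3 and 4). The outcome y_it "represents the proportion of the prescribed bottle openings that were opened by individual" i at time t. One T1 and one T2 coefficient are each interpreted as an effect "on the proportion of pills taken in a given month". The only time structure is lambda_t, which "represents an indicator for each time period". Eq. 4 adds baseline covariates. No random effect, person effect or GEE is given, and the error carries subscript i only.
- **Amount of repetition.** Under Percentage of prescribed medication taken, "MEMS data will be collected continuously during the 24 months of the intervention period". Eq. 5 sums over months up to 24.
- **Unit of randomization.** Study design states a three-arm trial "with randomization at the individual level".
- **Variance rule.** The Standard errors section is one sentence: "We will estimate Huber–White robust standard errors in all analyses".
- **Other statement on variance.** Handling missing data and attrition mentions design effects, but only those arising from nonresponse weights.

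**The concern.** A participant's arm does not change over the intervention months (although the indicators carry a t subscript), and a person's adherence in one month tends to resemble that person's adherence in the next. The article itself relies on such stability: it uses baseline adherence as a covariate to gain precision and as a subgroup factor. Repeated rows therefore add much less information on an arm difference than the same number of independent people would. With 330 participants and 24 months there are 330 × 24 = 7,920 rows before attrition, but only 330 randomized units.

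Ordinary Huber–White standard errors do not correct for this. At stake are the confidence intervals and p values for T1 against control, T2 against control and T2 against T1 on one of the two primary outcomes. The stated multiplicity adjustment covers secondary outcomes only, so it offers no buffer.

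**Working it through.** **1. The unit in the plan's own power figures.** Sample size and power starts from "Our sample size of 110 participants in each of the three arms", 80% power, a two-tailed test and 10% attrition per year. Alpha is not printed; 0.05 is assumed. Attrition leaves 110 × 0.9 = 99 per arm at month 12 and 99 × 0.9 ≈ 89 at month 24. The adherence SD is not printed either, so the detectable differences cannot be strictly reproduced. They can be solved for the SD they imply with one value per participant:

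SD = difference / [(1.960 + 0.842) × sqrt(1/n1 + 1/n2)]

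| Comparison | Stated difference (points) | n1, n2 | Implied SD (points) |
|---|---|---|---|
| T1+T2 vs control, month 12 | 6.5 | 198, 99 | 18.8 |
| T1 vs T2, month 12 | 7.5 | 99, 99 | 18.8 |
| T1+T2 vs control, month 24 | 7 | 178, 89 | 19.2 |
| T1 vs T2, month 24 | 8 | 89, 89 | 19.0 |

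The four agree at about 19 points. The power calculation is thus consistent with the participant as the unit, whereas Eqs. 3–4 with ordinary Huber–White errors take the person-month as the unit.

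**2. Size of the understatement.** For an arm effect constant within person, m months each and exchangeable correlation rho:

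- true SE / unclustered SE = f = sqrt(1 + (m − 1) × rho)
- actual error of a nominal 5% two-sided test = 2 × [1 − Phi(1.96 / f)]

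With m = 24:

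| rho (assumed) | 1 + 23 × rho | f | Type I error, formula | Type I error, simulated |
|---|---|---|---|---|
| 0.05 | 2.15 | 1.47 | 18% | 21% |
| 0.10 | 3.30 | 1.82 | 28% | 27% |
| 0.30 | 7.90 | 2.81 | 49% | 44%, 49% |
| 0.50 | 12.50 | 3.54 | 58% | 58%, 59% |

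The simulated column comes from two separate simulations of OLS with period effects and no true arm difference. One used 99 per arm with 300 runs per setting (rho 0.05, 0.30, 0.50); the other used 110 per arm with 2,000 runs per setting (rho 0.10, 0.30, 0.50). With participant-clustered errors, rejection was 3–7%.

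**3. Milder conditions.**

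- 12 months: f = sqrt(1 + 11 × 0.1) = 1.45 at rho 0.1, a type I error of about 18%. It cannot exceed sqrt(12) = 3.46.
- Decaying correlation over 24 months: simulated f was 1.67, 2.23 and 3.46 for AR(1) parameters 0.5, 0.7 and 0.9.
- Eq. 4 adjusts for baseline adherence, which lowers the residual rho by an amount the article does not allow one to compute. Eq. 3 has no such adjustment.

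**4. What is not affected.** The viral-suppression logistic models are fitted after year 1 and after year 2, with one row per person. A single-month contrast, as in Eq. 5, rejected a true null 4–7% of the time without clustering. A test combining several months of Eq. 5 would be affected.

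**The case against.** The strongest reply is that the Standard errors section does not say unclustered. The sandwich family has a cluster-robust form, the section neither names nor excludes it, and an article may leave the clustering level to a fuller analysis plan. The i-only error subscript and the participant-level power figures could be read as hints that the participant is the intended unit.

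Part of this stands: the article does not expressly rule clustering out, and the authors may intend it. It does not rescue the text. The article fixes one named estimator for every analysis, including logistic models with one row per person, where clustering has no role. The subscript supplies no clustering and may be a slip. The power figures show what the unit should be, which conflicts with the analysis as written.

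A second reply concerns size. A reader might infer that standard errors are simply two to four times too small, or that a false positive is more likely than not. The documents support neither, because they give no within-person correlation. With 24 months, a factor of 2 needs rho = 3/23 ≈ 0.13 and a factor of 4 needs rho = 15/23 ≈ 0.65. A type I error above one half needs f above 1.96/0.674 ≈ 2.91, hence rho above about (8.44 − 1)/23 ≈ 0.32, and it applies only if there is no true effect. Nor is the 24-month window stated for Eqs. 3–4; it is taken from the intervention period and from Eq. 5.

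**Conclusion.** The point holds for the pooled coefficients in Eqs. 3–4. Following the protocol article as written gives standard errors that are too small for the behavioural primary outcome, and nothing elsewhere in it allows for repeated months.

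The size is conditional on 24 months per person, exchangeable residual correlation and a 5% two-sided test. Over rho from 0.05 to 0.5 the understatement then runs from about 1.5-fold to 3.5-fold. It is smaller with fewer months, decaying correlation or baseline adjustment, and larger at higher rho. Even the mildest settings examined (rho 0.05 over 24 months, or rho 0.1 over 12 months) put a nominal 5% test at about 18%. The biological primary outcome and the individual monthly effects in Eq. 5 are not called into question.

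**What to change.** Replace the sentence under Standard errors with: *Standard errors will be clustered by participant in all models with repeated observations per participant (Eqs. 3–5), and Huber–White robust in models with one observation per participant.* Index the error in Eqs. 3–5 as epsilon_it.

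The cost is one sentence, a subscript and a software option. No new data or change of design is needed, and the stated adherence power figures already fit one value per participant. The downside is wider confidence intervals, which are the correct ones.

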##### Adjusting for multiple hypotheses

We will adjust *p* values for multiple hypothesis testing for all secondary outcomes specified above (and any ad hoc outcomes we analyze ex post) using the free step-down re-sampling method to control the false discovery rate [48].

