**Methods/design:**

We will enroll 330 HIV-positive patients at Mildmay Hospital in Kampala, Uganda, into a 2-year randomized controlled trial. Participants will be randomized to one of three groups. The first intervention group (T1, *n* = 110) will be eligible for small lottery prizes based on timely clinic visits and demonstration of viral suppression. Group 2 (T2, *n* = 110) will be eligible for the same lottery prizes conditional on high adherence measured by a medication event management system (MEMS) cap. The control group (*n* = 110) will receive the usual standard of care. Adherence will be measured continuously throughout the intervention period and for 12 months post-intervention to evaluate effect persistence. Surveys will be conducted at baseline and then every 6 months. Viral loads will be measured annually. Primary outcomes are whether the viral load is detectable and MEMS-measured adherence. Secondary outcomes are the log-transformed viral load as a continuous measure and a binary measure for whether the person took at least 90% of their ART pills.

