### Randomization

Randomization in a 1:1:1 ratio will occur after participants are recruited but before they complete a baseline survey to ensure that group assignment does not influence the answers given. We will stratify random assignment by age (under 25 or over 25), sex, marital status (married/cohabiting or unmarried), low CD4 count (below 200 or above 200), and viral load (detectable or undetectable). Stratified randomization is achieved by generating a separate block for each combination of covariates after identifying which clients fall into each block. We will then randomize treatment assignment within each block. We will use the *randtreat* package in Stata15 for the randomization procedure.

All clients recruited will complete the baseline survey approximately 2–3 months after recruitment. The client will be informed of their assignment to either one of the two intervention arms or the control group after completing the baseline survey.

Participants cannot be blinded to their treatment status and neither can interviewers. Interviewers are not blinded to treatment status when they read a MEMS cap. The data analyst who will conduct the impact analysis will be blinded to treatment assignment.

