### Outcomes

#### Primary outcomes

We have one biological primary outcome and one behavioral primary outcome.

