##### Estimating impact on viral suppression

We will use a logistic regression to compare the likelihood of viral suppression between the three study arms after year 1 and after year 2. We will estimate an unadjusted model and a model that includes prespecified covariates to adjust for baseline characteristics and improve precision. We will adjust for the following covariates: age, education, sex, baseline adherence, baseline WHO disease stage, baseline viral suppression, duration on ART, self-reported physical health, self-reported mental health, and HIV disclosure status.

Our main unadjusted model has the following form:
1$$ \Pr \left({y}_i\right)=\mathrm{expit}\left({\beta}_0+{\beta}_1T{1}_i+{\beta}_2T{2}_i+{\epsilon}_i\right) $$

and our main adjusted model has the following form:
2$$ \Pr \left({y}_i\right)=\mathrm{expit}\left({\beta}_0+{\beta}_1T{1}_i+{\beta}_2T{2}_i+{\boldsymbol{X}}_{\boldsymbol{i}}{\boldsymbol{\beta}}_{\mathbf{3}}+{\epsilon}_i\right) $$

where *y*_*i*_ is the probability of viral suppression of individual *i*, T1 is an indicator for treatment group 1, T2 is an indicator for treatment group 2, and *ϵ*_*i*_ is the idiosyncratic error. The coefficients of interest are *β*_1_ and *β*_2_. Equation 2 has the term ***X***_***i***_***β***_**3**_, which includes a vector of the prespecified covariates described above (***X***_***i***_) and the respective coefficients (***β***_**3**_). We will estimate the marginal difference (or risk difference) between each of the three study arms as the following:
$$ \mathbbm{E}\left[{y}_i\right|T1=1\left]-\mathbbm{E}\left[{y}_i\right|\mathrm{Control}=1\right] $$: Impact of treatment 1 on the outcome relative to the control group$$ \mathbbm{E}\left[{y}_i\right|T2=1\left]-\mathbbm{E}\left[{y}_i\right|\mathrm{Control}=1\right] $$: Impact of treatment 2 on the outcome relative to the control group$$ \mathbbm{E}\left[{y}_i\right|T2=1\left]-\mathbbm{E}\left[{y}_i\right|T1=1\right] $$: Impact of rewarding adherence relative to rewarding viral suppression

We will also estimate a model where we pool T1 and T2 (relative to the control group) to estimate the impact of lottery incentives more generally.

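### The secondary-outcome adjustment is open to outcomes added after the data are seen, so the verdict on the two pre-specified secondary outcomes can be diluted by later choices

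*Protocol article*

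**What the plan says.** Under Adjusting for multiple hypotheses, one sentence sets both the scope and the method. The adjustment is for "multiple hypothesis testing for all secondary outcomes specified above (and any ad hoc outcomes we analyze ex post", carried out "using the free step-down re-sampling method to control the false discovery rate".

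The secondary outcomes are named in the abstract: "Secondary outcomes are the log-transformed viral load as a continuous measure and a binary measure for whether the person took at least 90" percent of the ART pills. That makes two. The Outcomes section of the body lists only the primary outcomes ("We have one biological primary outcome and one behavioral primary outcome"), and these are not in the adjustment.

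The article does not limit the number of ad hoc outcomes, give them a separate family, or rank them behind the pre-specified outcomes. It does not state alpha, the size of the family, or which contrasts and time points of the secondary outcomes enter it.

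**The concern.** In a step-down resampling procedure, the adjusted p value of the smallest raw p is the null probability that the minimum p over the whole family is at or below it. The family is therefore part of the decision rule. If outcomes can join it after results are known, the rule for the two pre-specified outcomes is not fixed in advance. Two teams with identical data on log viral load and 90% adherence could report different conclusions because one of them also looked at more outcomes.

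At stake are the power of the two secondary outcomes and how firmly their conclusions are fixed. Adjusting ad hoc outcomes is good practice; the weakness is that they share an adjustment with outcomes chosen beforehand.

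**Working it through.** The article gives no figure for this adjustment, so there is nothing to reproduce. The check is of the mechanism and its likely size.

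**Inputs from the article**
- Two pre-specified secondary outcomes (abstract).
- One step-down resampling procedure covering these and the ad hoc outcomes (Adjusting for multiple hypotheses).
- Two-sided testing: "80% power (two-tailed test" (Sample size and power).

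**Assumptions, not in the article**
- Alpha 0.05 and one test per outcome.
- 5 or 10 added outcomes, giving m = 7 or 12 in all.
- Equal correlation of 0, 0.5 or 0.8 between test statistics.
- 80% unadjusted power for a secondary outcome. The article powers only viral suppression and mean adherence.

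**Direction.** At each step, the adjusted p is P(min p over the outcomes still in the set ≤ the observed p), and a running maximum is taken over steps. Adding an outcome enlarges each set, which cannot lower the probability, and adds a step to the maximum, which cannot lower it either. So a pre-specified outcome's adjusted p rises or stays the same, whatever is added.

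**Size, raw p = 0.01 and smallest in the family.** For independent outcomes, adjusted p = 1 − 0.99^m:
- m = 2: 1 − 0.9801 = 0.020
- m = 7: 1 − 0.9321 = 0.068
- m = 12: 1 − 0.8864 = 0.114

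For correlated outcomes the same probability was obtained by simulation and confirmed by numerical integration:

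| Correlation | m = 2 | m = 7 | m = 12 |
|---|---|---|---|
| 0 | 0.020 | 0.068 | 0.114 |
| 0.5 | 0.019 | 0.055 | 0.083 |
| 0.8 | 0.017 | 0.036 | 0.047 |

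**Power at the first step**, for an effect with 80% unadjusted power. The mean of the test statistic is 1.96 + 0.84 = 2.80, and power is Φ(2.80 − c), where c is the 95th percentile of max|Z| over the m outcomes:

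| Correlation | m = 2 | m = 7 | m = 12 |
|---|---|---|---|
| 0 | 71% | 55% | 48% |
| 0.5 | 72% | 57% | 51% |
| 0.8 | 74% | 64% | 60% |

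**A second scenario.** The two secondary outcomes have raw p = 0.02 and 0.04; all outcomes are independent and any added ones are unremarkable.
- None added: 1 − 0.98^2 = 0.040 for the first. The second is the larger of 0.040 and 0.04, so 0.04. Both pass 0.05.
- One added: 1 − 0.98^3 = 0.059, then 1 − 0.96^2 = 0.078. Both fail.
- Three added: 1 − 0.98^5 = 0.096, then 1 − 0.96^4 = 0.151.

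At correlation 0.7, one addition gives 0.046 and 0.067 (one result lost), and three give 0.066 and 0.107 (both lost).

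**Sensitivity to the baseline.** For viral suppression, the plan is to "compare the likelihood of viral suppression between the three study arms after year 1 and after year 2", with three pairwise contrasts and a pooled one. If the secondary outcomes followed that pattern, the pre-specified family would hold 2 × 4 × 2 = 16 tests. A raw p of 0.01 would then adjust to 1 − 0.99^16 = 0.149 (independent) with nothing added. Five further single tests would bring it to 1 − 0.99^21 = 0.190, a factor of 1.3. From a base of two tests, five additions give 0.068/0.020, a factor of 3.4.

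**The case against.** The strongest reply is that the article never says the two sets form one family. It names a method and applies it to both, the second in parentheses, and drawing families is often left to an analysis plan. That stands as a point about wording. Still, one sentence with one procedure most naturally means one adjustment, and nothing else in the article separates the sets.

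A reader might infer that error control for the secondary outcomes is lost, or that added outcomes could make a secondary outcome significant. Under the named method the documents do not support this. The direction argument shows that additions only raise or preserve the adjusted p, so the error for the two outcomes stays within that of the closed family. Additions could help only under a true false-discovery-rate procedure. With Benjamini-Hochberg, for example, a raw p of 0.03 beside 0.5 adjusts to 2 × 0.03 = 0.060 alone, and to 3 × 0.03/2 = 0.045 with one strong ad hoc outcome. The article does attach a false-discovery-rate label to a step-down resampling method that controls familywise error. That mismatch is a separate matter, and this point does not rest on it.

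A reader might also infer that ad hoc outcomes are given confirmatory standing. The article does not say so; its own wording marks them as ad hoc and after the fact.

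Two further replies limit the consequence. The figures rest on assumed family sizes, correlations and alpha, and if more tests are already in the family, each single added test matters less. The article also says: "The data analyst who will conduct the impact analysis will be blinded to treatment assignment". This makes selection in favour of one arm harder, but it does not fix which outcomes enter the family.

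**Conclusion.** The point holds as a modest weakness in a stated rule, confined to the secondary outcomes. Read naturally, the plan lets outcomes chosen after the data are seen raise the adjusted p values of two pre-specified outcomes and lower their power. The harm is dilution and a verdict not fixed in advance, not inflated false positives.

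The size cannot be determined from the article. Under the stated assumptions, five to ten additions can carry a raw p of 0.01 past 0.05 at correlations of 0 and 0.5, but not at 0.8, where it reaches 0.047. First-step power falls from 71–74% with two outcomes to 48–60% with twelve. No primary conclusion changes.

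**What to change.** Reword Adjusting for multiple hypotheses to state three things:
- The adjusted secondary family is closed and consists of log viral load and the 90% adherence indicator.
- The contrasts and time points tested for each are listed in advance.
- Ad hoc outcomes are adjusted in a separate family, labelled exploratory, which does not enter the adjustment of the pre-specified outcomes.

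The cost is about one sentence plus the list of contrasts and time points, with no extra data or visits. The article reports recruitment as still under way, so at that stage the change could precede any outcome analysis. The downside is that ad hoc outcomes are reported as exploratory only.
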